# Implementation and effectiveness of a nurse-enabled, shared-care follow-up model for early breast cancer survivors (The IBIS-Survivorship Study): protocol for a stepped-wedge cluster randomised trial

**DOI:** 10.1136/bmjopen-2025-103341

**Published:** 2025-06-19

**Keywords:** Primary Care, Breast tumours, Nursing Care

## Abstract

**Introduction:**

Breast cancer is the most commonly diagnosed cancer among women worldwide. Survivors often experience physical and psychological effects arising from breast cancer and its treatment, which can last months and years, adversely impacting quality of life. As the number of early breast cancer survivors increases, models of specialist-led follow-up care in hospital settings are not sustainable and evidence suggests that they may not meet survivors’ needs. Nurse-enabled, shared-care, follow-up models between cancer specialist and primary care teams have potential to address this need.

**Methods and analysis:**

The proposed research is a multicentre, prospective, pragmatic, stepped-wedge cluster-randomised trial designed to test the effectiveness and implementation of *IBIS-Survivorship*, a follow-up care model for patients with early breast cancer who have completed primary treatment. The *IBIS-Survivorship* intervention involves a nurse-led consultation, development of a Survivorship Care Plan and case-conferencing between a breast care nurse and the patient’s primary care provider. This study seeks to recruit 1079 breast cancer survivors across six cancer centres (clusters) in Australia. Health-related quality of life at 12 months assessed by the Functional Assessment of Cancer Therapy - Breast Cancer questionnaire will be the primary endpoint, along with a range of patient-reported outcomes, safety indicators and cost-effectiveness measures as secondary endpoints. General and generalised linear mixed models will be used to assess the effectiveness of the intervention versus usual care. Implementation and process outcomes will be assessed using the Reach Effectiveness Adoption Implementation Maintenance framework.

**Ethics and dissemination:**

Ethical approval was provided by the Metro South Hospital and Health Service Human Research Ethics Committee (HREC/2020/QMS/59892) and reciprocally across the other five trial sites under National Mutual Acceptance arrangements. Results will be disseminated through peer-reviewed academic journal publications and presentations at national and international conferences.

**Trial registration:**

Australia and New Zealand Clinical Trials Registry (ANZCTR) Trial ID: ACTRN12621000188831.

STRENGTHS AND LIMITATIONS OF THIS STUDYThe IBIS-Survivorship model is a complex intervention intended to take a coordinated approach to implementing shared care follow-up that can be tailored to the needs of individual patients.The hybrid effectiveness-implementation design will evaluate the IBIS-Survivorship shared care follow-up model in diverse breast cancer clinic settings.Each cluster has different practicalities in follow-up care to suit their unique setting. A strength of using the stepped-wedge cluster-randomised trial design allows for the evaluation of service delivery without contamination between intervention and control clusters.The study was limited to six clusters due to practical constraints.Collection of patient-reported outcomes, health service utilisation and qualitative data will gather extensive insights into both effectiveness and implementation outcomes.

## Introduction

 Breast cancer is the most commonly diagnosed cancer in Australian women and worldwide, with 5-year survival rates in Australia at 92%.^1 2^ This high survival rate means there is a growing number of people requiring ongoing care after treatment completion for breast cancer to manage a variety of long-term biopsychosocial effects from the cancer diagnosis and treatment.^3^ Furthermore, many cancer survivors, including those diagnosed with breast cancer, have comorbid conditions that require ongoing management.^4^ Cancer survivors are more likely to develop circulatory, musculoskeletal and endocrine system disorders and psychological and behavioural problems compared with those without a cancer diagnosis.^4^ The breadth of these concerns accentuates the need for seamless, multidisciplinary, patient-centred care following the completion of primary breast cancer treatment in order to comprehensively address patient needs.^5^ In Australia, predominant models of post-treatment follow-up care for breast cancer are hospital-based and driven by oncology specialists, focusing on surveillance for disease recurrence rather than addressing personalised survivorship care needs. Such models are not sustainable and limit coordination of care between oncology specialist services and primary care.^6 7^ With an ever-growing population of breast cancer survivors, there is a need for a coordinated pathway of post-treatment care involving oncology specialists and primary care teams.^8^

A shared care model for early breast cancer follow-up is consistent with Australian policies including Cancer Australia guidelines^9^ and the Optimal Care Pathway for breast cancer,^5^ as well as international recommendations.^10^ Shared care is follow-up after treatment completion that is shared between a hospital-based specialist team and primary care provider, usually a general practitioner (GP—Australian primary care physician) where both parties have ongoing involvement in the patient’s care. For many cancer survivors, such a model has been demonstrated to be safe, effective, acceptable, cost-efficient and more patient-centred.^11 12^ For example, a Canadian multicentred, randomised controlled trial of patients who completed treatment for early breast cancer (n=968) concluded that follow-up care led by primary care providers was safe and there were no differences in recurrence-related serious clinical events.^13^ Similar Australian studies have concluded that shared care between oncology specialists and GPs is feasible, acceptable and as safe as specialist-led models.^14 15^ Importantly, shared care models demonstrate similar effectiveness to usual care (ie, specialist-led care) in terms of patient quality of life.^1115^,^17^ GPs are well placed to address psychosocial issues, promote healthy lifestyle behaviours and address comorbid health conditions compared with oncology specialists.^14^ Additionally, an economic modelling study indicated that shared care is more cost-effective than specialist-led care and could save over $A3.5 million for the 500 patients in this study over 5 years by releasing specialist time for more urgent cases, relieving pressure on the acute care system.^14^

Although the evidence for shared care models in early breast cancer is promising, these models are not routinely implemented into practice in Australia, as barriers such as lack of role clarity, inadequate support to transfer care and information across acute care and primary care systems and communication difficulties impact on successful implementation.^18^ Research has investigated the role of nurse-led models of survivorship care, highlighting that nurse-led care can improve quality of life^19^ and produce cost savings to cancer survivors and healthcare systems.^8^ Specialist cancer nurses in the hospital setting (experienced registered nurses who have received additional training to make them an expert nurse in cancer care) are well-placed to facilitate effective and timely care and communicate with GPs in a shared care model.^20 21^ In Australia, BCNs have provided information and support to patients, as well as co-ordinating patient care, since the ‘90s,^22^ with access to these nurses resulting in an improved experience for patients and families.^23^ Therefore, the opportunity exists for BCNs to contribute further to shared care planning and follow-up care.^23^

The aim of this study is to assess both the effectiveness and implementation of a nurse-enabled shared care follow-up model (*IBIS-Survivorship*) for cancer survivors who have completed primary treatment for early breast cancer in Australia via a stepped-wedge cluster randomised trial (SW-CRT). To our knowledge, there are no SW-CRTs in shared care for patients with early breast cancer that evaluate the effectiveness and implementation of a shared care model of follow-up.

## Methods and analysis

This study protocol (V.2.4) was written in accordance with the Standard Protocol Items: Recommendations for Interventional Trials guidelines^24^ (see online supplemental material A).

The proposed study will use a SW-CRT design to deliver the *IBIS-Survivorship* model sequentially in six acute care cancer centres across metropolitan and rural Australia. *IBIS-Survivorship* is a multicentre, prospective, pragmatic type II hybrid effectiveness-implementation trial of a nurse-enabled shared care model. Our primary hypothesis is that participants receiving the *IBIS-Survivorship* intervention will have a significantly better breast cancer-specific health-related quality of life (HRQoL) at 12 months post enrolment, compared with those receiving usual care. Secondary hypotheses are that participants receiving *IBIS-Survivorship* will have higher satisfaction with care; higher uptake of healthy lifestyle behaviours and equivalent adherence to annual mammography, annual physical examination and endocrine therapy at 12 months post enrolment. It is, however, acknowledged that the collection of these adherence outcomes for the longer term will require additional resources to follow patients. We also hypothesise that *IBIS-Survivorship* will be more cost-effective compared with usual care. Implementation and process outcomes will be assessed using the Reach Effectiveness Adoption Implementation Maintenance (RE-AIM) Framework.^25^

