	Satisfaction of care	0–10 numerical analogue scale (with 10 being the most satisfied) supplemented with short qualitative interviews.			✓	✓
	Unplanned hospital admissions	Self-report (verified with hospital records)		✓	✓	✓
	Adherence to annual mammogram, physical breast exam and endocrine therapy	Hospital records			✓	✓
Cancer Centre	Reach and representativeness					
	Demographics	Self-report: age, gender, ethnicity, education, living arrangements, marital status, children (including ages) and employment	✓			
	Medical history	Hospital records and self-report: Previous cancer diagnoses and treatments	✓			
	Clinical characteristics	Hospital records and self-report: Breast cancer diagnosis and treatment protocols received	✓			
	Adoption and maintenance (sustainability)					
	% GPs explicit engagement in case conference	Records in database				✓
	Implementation					
	Completion (Y/N) and duration (min) of BCN-led consultation	BCN records, completion of the BCN-led consultation checklist and RN records in database				✓
	Completion (Y/N) and duration (min) of Case Conferencing with GP	BCN records, completion of the GP Case-conference checklist.				✓
	Completed survivorship care plan/components (Y/N)	BCN records, Survivorship Care Plans				✓
	Completed Chronic Disease Management plan (Y/N)	MBS (by GP)				✓
	No. and timing of GP visits and specialist visits	MBS and patient self-report (verified with hospital records)				✓
	Health provider satisfaction	Semistructured interviews				✓
	Economic appraisal					
	Cost-effectiveness	Self-report: The EQ-5D-5L is a standardised measure of health status developed by the EuroQol Group to provide a simple, generic measure of health for clinical and economic appraisal.^55^ The EQ-5D 5 L is a valid, reliable and responsive instrument with published Australian value sets for calculating quality-adjusted life years	✓	✓	✓	

T1=baseline/enrolment; T2=6 months post enrolment; T3=12 months post enrolment.

BCN, Breast Cancer Nurse; CDM, Chronic Disease Management plan; EQ 5D-5L, EuroQol 5 Dimensions 5 Levels; GP, primary care physician; MBS, Medicare Benefits Scheme; RE-AIM, Reach, Effectiveness, Adoption, Implementation and Maintenance.

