### Sample size

The sample size is fixed by the number of clusters, the study duration and funding constraints. Initially, it was expected that seven cancer centres (clusters) would participate in the study; however, one cancer centre was unable to participate due to COVID-19 impacts on the health service, thus the sample size calculation and randomisation were determined after the number of clusters was confirmed as six. It is anticipated that the total number of available patients with early breast cancer will be 1384; split across the six clusters and nine cluster periods in the design. Assuming 22% of patients cannot identify a regular GP or decline participation (based on Cancer Australia’s pilot study),^29^ the potential sample size for recruitment is 1079. We will also allow for attrition of 30% by 12 months or T3 (conservative estimation based on the PROCARE Trial),^16^ thus the expected sample size for patient-reported data collection at T3 is 755 (equivalent to an average of 13 per cluster period and 125 per cluster, although varying cluster sizes are expected).

Using the online RShiny App,^41^ we estimated the power to detect a minimum clinically important difference in primary outcome (FACT-B mean scores at 12 months) between groups, of 8 points and a SD of 19 (total score possible=148), with a 2-sided type I error rate of 0.05. There is little information to support likely values of the intracluster correlation coefficient (ICC), the cluster autocorrelation coefficient (CAC) and the coefficient of variance (CV), so values were estimated from the literature. We allowed for clustering (assuming a within-period ICC of 0.03 and CV of 0.3) and for varying cluster sizes.^35^ To explore sensitivity, ICC estimates of 0.03 (0.005–0.05)^25^ and CV estimates of 0.3 (0.1–0.5) were used. Due to the longitudinal nature of this trial, correlations may differ in the same cluster period and in different cluster periods. Adjustment for time-varying correlations is made using a discrete time decay correlation structure, and the CAC is used to adjust for the correlation between two means in the same cluster at different times. Sensitivity of the CAC was explored using scores of 0.8 (0.6–0.9) in power calculations.^26^ Under these assumptions, the power curves reveal that under most anticipated scenarios, the trial will have 90% power in some conservative but plausible scenarios.

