#### Analysis of effectiveness outcomes

Analyses will be conducted as intention to treat, and clusters will be considered exposed to the intervention postrandomised crossover date. This will include all eligible patients for whom data have been obtained, from enrolment to 12 months. Data will be analysed with respect to the treatment specified for each cluster by the allocated randomisation order.

The primary and secondary continuous outcomes will be analysed using a linear mixed model with an identity link function using a restricted maximum likelihood approximation with a Kenward-Roger approximation which is suitable for small samples.^42 43^ Results will be presented as mean differences between groups with 95% CIs.

The primary outcome will be assessed in a model which will include a random cluster effect, a fixed effect for period (1-9) and a random cluster by period effect to test the difference in means between groups (usual care vs intervention) for FACT-B scores at 12 months. This will estimate the time-averaged effect of the intervention. The random cluster by period interactions will allow for correlations within clusters to decay with increasing separation between times of measurement of observations. Adjustments will be made for the baseline FACT-B scores (as a covariate) and for factors used in the randomisation procedure (metropolitan vs regional location of cancer centre).

Sensitivity analyses will be conducted to estimate the effect of time since exposure, where time since exposure is a fixed effect (1-8). This will assess the effect of the intervention after one period of exposure, two periods of exposure and up to eight periods of exposure compared graphically in forest plots. Additional sensitivity analyses will adjust for patient level covariates (eg, age, education, living arrangement, disease or treatment variable and number of comorbidities) based on expert clinical guidance. The selection of baseline characteristics is based on clinical concern for imbalance between intervention groups or variables that are most prognostic of the outcome.

Similar analyses will be conducted for all secondary outcomes at 6 months and 12 months, including analysis of the difference in means between groups for FACT-B scores at 6 months. Results will be presented as mean differences between groups with 95% CIs.

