A per protocol analysis will be completed for primary and secondary outcomes of the trial, which will exclude departures from randomisations such as participants randomised to receive the intervention who did not receive the intervention. These participants will be removed from the analysis. The two key components of the intervention (nurse-led consultation and GP case conference) will be considered intervention ‘doses’ and the per protocol analysis will be used to compare groups who completed either the full intervention or half the intervention with those on usual care. A further analysis will use the actual cluster cross-over date if there is variation from the proposed crossover date.

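### Equivalent adherence is hypothesised, but the stated analysis is of the difference type with no margin or interval rule, so as written it cannot establish equivalence

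*Protocol article*

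**What the plan says.** The Methods and analysis section of the protocol article words its hypotheses by direction: better quality of life, higher satisfaction, higher uptake of healthy behaviours. For adherence it instead expects "equivalent adherence to annual mammography, annual physical examination and endocrine therapy at 12 months post enrolment". Table 2 lists "Adherence to annual mammogram, physical breast exam and endocrine therapy" among the secondary effectiveness outcomes, taken from hospital records.

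Under Analysis of effectiveness outcomes, the primary model is fitted "to test the difference in means between groups (usual care vs intervention) for FACT-B scores at 12 months". The section then says "Similar analyses will be conducted for all secondary outcomes at 6 months and 12 months" and adds "Results will be presented as mean differences between groups with 95% CIs". Adherence is not exempted. The section also says "A per protocol analysis will be completed for primary and secondary outcomes of the trial", but links that analysis to no equivalence conclusion.

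The Sample size section addresses only the FACT-B difference, "with a 2-sided type I error rate of 0.05". The article gives no margin, expected adherence rate or power for the adherence hypothesis.

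**The concern.** Equivalence is a different claim from the absence of a detected difference. It needs a margin fixed in advance and an interval shown to lie inside it. The article states the claim and describes an analysis, but the analysis has no element that could confirm the claim.

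With six clusters the adherence intervals will be fairly wide. A drop in mammography, examination or endocrine therapy adherence large enough to matter could pass as non-significant, and a reader could take that as support for the hypothesis. At stake is whether the trial may say that adherence is maintained under shared follow-up.

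**Working it through.** **Inputs from the article.** 1384 available patients, 22% not recruited, 30% attrition; six clusters; enrolment in seven of the nine periods, with one cluster crossing over per period; within-period ICC 0.03 (range 0.005 to 0.05); CAC 0.8 (range 0.6 to 0.9) with discrete time decay; FACT-B difference 8, SD 19.

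**Assumptions.** Adherence is yes/no at 80%, 90% or 95%; the article gives no rate. ICC and CAC are the FACT-B values carried over to adherence. All 1079 participants have usable records. Cells are equal and quantiles normal. The ±5 and ±10 point margins only show scale and are not proposals.

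**The plan's own figures.** 1384 × 0.78 = 1079.5 and 1079 × 0.70 = 755.3, matching the stated 1079 and 755. The treatment-effect variance comes from generalised least squares with fixed period effects. The covariance of cell means within a cluster is SD² × ICC × CAC^|t−s|, plus SD² × (1 − ICC)/m on the diagonal, where m is the cell size. With m = 755/42 ≈ 18, the standard error is 0.129 × 19 ≈ 2.45. Power is Φ(8/2.45 − 1.96) = Φ(1.31) ≈ 90%, which agrees with the stated 90%.

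**Interval width for adherence.** With m = 1079/42 = 25.7, the standard error is 0.114 × SD, where SD = √(p(1−p)). The half-width is 1.96 × SE. The chance that a true 5-point fall is non-significant is Φ(1.96 − 5/SE), with SE in points; the opposite tail is negligible.

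| Assumed adherence | SD | SE (points) | 95% half-width (points) | Chance that a true 5-point fall is non-significant |
|---|---|---|---|---|
| 80% | 0.400 | 4.56 | 8.9 | 81% |
| 90% | 0.300 | 3.42 | 6.7 | 69% |
| 95% | 0.218 | 2.49 | 4.9 | 48% |

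**Sensitivity at 90% adherence.** Over ICC 0.005 to 0.05 the last column runs from 55% to 73%. At CAC 0.6 and 0.9 the multiplier of SD becomes 0.118 and 0.109, giving half-widths of about 6.9 and 6.4 points. Allowing for unequal cluster sizes (CV 0.3) gives 6.8. If only 755 records were usable, with CV 0.3, the half-width is 7.7 and the chance of non-significance 75%.

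**Chance of showing equivalence when there is truly no difference (90% adherence).** The chance that the whole 95% interval lies within ±M is 2Φ(M/SE − 1.96) − 1, or zero if the half-width exceeds M.

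- M = 10: 2Φ(10/3.42 − 1.96) − 1 = 2Φ(0.96) − 1 ≈ 66%.
- M = 5: the half-width of 6.7 exceeds 5, so 0%.

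Two one-sided 5% tests, which use a 90% interval, give about 79% at ±10 (with CV 0.3) and still 0% at ±5. A small-sample correction for six clusters would lower all of these chances.

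**The case against.** The strongest reply is that the article offers only an overview of the statistical analysis plan, and that a margin for one secondary outcome is the sort of detail it may leave there. A difference with a 95% interval is also the quantity an equivalence assessment uses, so only the margin is absent. This has some force: the unseen plan may contain a margin. But the article does describe the secondary analysis, applies it to every secondary outcome and models it on a test of difference. The hypothesis and the analysis it states therefore do not meet, and that can be corrected in this document.

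Three stronger readings are tempting and are not supported:

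- **A null result will be read as equivalence.** The article states no such rule. It promises estimates with intervals. The misreading is possible, not planned.
- **Yes/no outcomes are to be analysed with a linear model.** The linear mixed model is confined to continuous outcomes, and the abstract says "General and generalised linear mixed models will be used to assess the effectiveness of the intervention versus usual care". What remains is that reporting mean differences is loose wording for a yes/no outcome.
- **Adherence is the trial's main safety evidence.** Unplanned admissions are also collected and checked against hospital records. Table 1 keeps the annual mammogram and full physical examination with the oncology specialist in the intervention arm.

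It is also fair to object that the size rests on assumed adherence rates and borrowed correlation values. Endocrine therapy adherence may apply only to participants prescribed it, which would widen its interval.

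**Conclusion.** The concern holds as a mismatch between a stated hypothesis and a stated analysis. The article claims equivalence for three adherence outcomes, and nothing in the analysis it describes could establish that.

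Under the assumptions above, a non-significant difference would be weak evidence. A true 5-point fall would be missed about 81% or 69% of the time at 80% or 90% adherence, and about half the time at 95%. At 90% adherence the design has a moderate chance (about 66%) of placing the interval within ±10 points and none of placing it within ±5.

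The exact figures depend on adherence rates the article does not give. The mismatch does not depend on them. It concerns a secondary hypothesis and leaves the primary FACT-B analysis untouched.

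**What to change.** Choose one of two changes.

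1. Reword the hypothesis: the trial will estimate the difference in adherence with a 95% confidence interval and will make no claim of equivalence.
2. Before database lock, fix a justified margin for each of the three adherence outcomes. Claim equivalence only if the whole 95% interval of the adjusted risk difference from the generalised mixed model lies inside it. If only a loss of adherence matters, restate the hypothesis as non-inferiority and judge it on the lower limit. Report the intention-to-treat and per-protocol results together.

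In either case, state that a non-significant difference will not be reported as equivalence, and name the effect measure for these outcomes. If the statistical analysis plan already holds a margin, cite it in the hypothesis.

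The cost is one reworded hypothesis or one decision rule, with no new data. The downside is that the trial may not be able to claim equivalence, particularly with a narrow margin.
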